**Table 8 Safety Statistical Analysis Methods**

**Endpoint Statistical Analysis Methods**

Adverse events The original terms recorded on the eCRF by the Investigator for AEs will be coded by the Sponsor.

AEs will be summarized by mapped term and appropriate thesaurus level. Incidence, nature and severity of AEs, number of participants with SAEs, treatment-related SAEs, SAEs leading to discontinuation, treatment-related AEs, or AEs leading to discontinuation will be tabulated and/or listed, as appropriate.

Clinical laboratory tests

All clinical laboratory data will be stored on the database in the units in which they were reported. Laboratory test values will be presented in International System of Units (SI units; Système International d’Unités) by individual outputs with flagging of abnormal results. In addition, tabular summaries will be used, as appropriate. Laboratory data not reported in SI units will be converted to SI units before processing.

Vital signs Vital signs data will be presented with flagging of values outside the normal ranges and flagging of abnormalities. In addition, tabular summaries will be used, as appropriate.

ECG data analysis ECG data will be tabulated and/or listed, as appropriate.

Concomitant medications

The original terms recorded on the participants’ eCRF by the Investigator

for concomitant medications will be standardized by the Sponsor by utilizing a mapped term and appropriate drug dictionary level.

Concomitant medications will be presented using appropriate outputs.

AE = adverse event; ECG = electrocardiogram; eCRF = electronic case report form; SAE =

serious adverse event.

**9.4.4 Pharmacokinetic Analyses**

Pharmacokinetic parameters will be read directly from the plasma concentration-time profiles or calculated by using standard non-compartmental methods. The following PK parameters will be computed for RO7486967 and its metabolites as applicable. However, other PK parameters might be computed in addition as appropriate:

• Time to maximum concentration (Tmax) after the dose on Day 1, and at steady-state.

• Maximum concentration (Cmax) measured post the dose on Day 1, and at steady- state.

• Concentration measured at the end of the dosing interval prior to the next study treatment administration (Ctrough), when applicable.

• Area under the serum concentration-time curve after the first dose administration extrapolated to infinity (AUCinf) and over the dosing interval (AUCtau) at steady-state (where tau=24 hours). If deemed useful, a partial AUC0-t may be used instead of AUCinf or AUCtau should extrapolation to infinity or up to tau not be considered reliable.

• Apparent clearance after the first dose administration (CL/F = dose/AUCinf) as well as at steady-state (CLss/F = dose/AUCtau).

• Apparent volume of distribution (V/F) after the first dose administration.

• Estimates of T1/2 after the first dose administration.

To evaluate drug accumulation, individual as well as mean (standard deviation) of apparent peak and trough (predose) after each dose administration will be plotted graphically over the course of assessments. In addition, AUCtau post the dose on Day 1, or alternatively a partial AUC0-t , will be tested statistically against AUCtau (or alternatively AUC0-t ) post the dose on the day of the final dose using an analysis of variance with terms in the model for participants and day. A natural log transform of the data will be done prior to the analysis.

Individual and mean plasma and gut tissue concentrations at each sampling time point for RO7486967 will be presented by listings and descriptive summary statistics including arithmetic means, geometric means, ranges, standard deviations, and coefficients of variation. Individual and mean plasma concentration versus time will be plotted on linear or semi-logarithmic scales as appropriate.

All PK parameters will be presented by individual listings and summary statistics including arithmetic means, geometric means, medians, ranges, standard deviations, and coefficients of variation.

In addition to the non-compartmental method, a population PK analysis using non-linear mixed effects modeling (NONMEM, Version 7.4 or higher) will be performed including pooled data from multiple studies to analyze the plasma concentration-time data of RO7486967 following oral administration. The analysis methods and results of the population PK modeling will be reported separately.

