**2.2.2 RO7486967**

The results of the entry-into-human (EIH) Phase 1 study IZD334-001 showed that RO7486967 appeared to be safe and well tolerated when administered to healthy male and female adult volunteers at single-ascending doses of 20 mg, 60 mg (fasted and fed),

180 mg, 450 mg, and 600 mg; and multiple-ascending doses (MAD) of 180 mg once daily (QD), 180 mg twice daily, and 450 mg QD for 7 days. The PK results showed rapid absorption of RO7486967, a half-life of approximately 7 hours, and no indication of a change in the exposure on repeat dosing for 7 days. The PD results showed that RO7486967 achieved the desired inhibition of IL-1β ex vivo whole blood lipopolysaccharide (LPS) and nigericin-induced IL-1β release assay.

A detailed description of the chemistry, pharmacology, and safety of RO7486967 is provided in the IB.

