**4. STUDY DESIGN**

**4.1 OVERALL DESIGN**

Study BP43099 is a randomized, placebo-controlled, Investigator- and patient-blind, Sponsor-open study to assess safety, tolerability, and PK of RO7486967 in patients with active, moderate to severe UC. The study will utilize two treatment arms: placebo versus

450 mg RO7486967 administered orally QD.

A total of 18 participants are expected to be recruited, with approximately 12 receiving

450 mg RO7486967 and approximately 6 receiving placebo.

All participants in the study will have been diagnosed with UC previously and be in an active stage of their disease.

After the screening period, participants will be randomized to receive either placebo or RO7486967 orally (3 capsules of 150 mg). Randomization will be 2:1 (RO7486967 to placebo) and occur on Day −1. Treatment duration will be 7 days. Participants will have biopsies taken from the rectum (rectoscopy) between Day −3 and Day −1 and on Day 7 pre-dose (see Figure 1).

Participants will be hospitalized from Day −1 to Day 7. They will return to the clinic for the follow-up visit on Day 14 ± 3 days.

Dose adjustments are not foreseen during the study.

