**8.4 PHARMACOKINETICS**

Blood samples will be collected to determine plasma concentration of RO7486967 and its metabolites, as appropriate. Samples will be collected at the timepoints specified in the SoAs (Section 1.3).

The timings of sample collection may be amended during study conduct on the basis of emerging data in order to allow optimal characterization of the PK profile.

Plasma concentrations of RO7486967 (and its metabolites as applicable) will be measured by a specific and validated LC-MS/MS method. Leftover samples may be used for exploratory analyses and may also be used for assay development/validation experiments.

Samples collected from placebo-treated participants will not be analyzed in the first instance, but retained for subsequent analysis if appropriate.

Samples will be destroyed within 2 years after the date of final clinical study report

(CSR).

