**9. STATISTICAL CONSIDERATIONS**

**9.1 STATISTICAL HYPOTHESES**

No statistical hypotheses are to be tested in this study.

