**9.2 SAMPLE SIZE DETERMINATION**

The study is expected to enroll approximately 18 patients in total, with 6 in the placebo arm and 12 in the treatment arm.

No formal statistical sample size calculations were performed; sample size is based on feasibility. No formal statistical analyses will be undertaken. Data will be summarized and listed as appropriate.

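### Section 9.4.4 adds a significance test to its accumulation plots but plans no accumulation ratio or interval, which conflicts with Sections 9.1 and 9.2 and leaves the size of any rise without a stated precision

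*Combined protocol and SAP*

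**What the plan says.** PK in blood is a primary objective (Table 3). Accumulation is not named there as an endpoint; it is one of the PK analyses in Section 9.4.4. That section evaluates it in two ways:

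- Individual and mean (SD) peaks and troughs are plotted over the course of the study.
- In addition, AUCtau after the Day 1 dose, or a partial AUC, "will be tested statistically against AUCtau (or alternatively AUC0-t ) post the dose on the day of the final dose using an analysis of variance". The model terms are participant and day, and AUC is analysed on the natural log scale.

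Section 9.4.4 also lists and summarises every PK parameter, including by geometric mean. It gives no alpha, no Day 1 to later-day ratio, no confidence interval and no margin. A pooled population PK analysis is planned but reported separately.

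Section 9.1 says: "No statistical hypotheses are to be tested in this study". Section 9.2 says: "No formal statistical analyses will be undertaken. Data will be summarized and listed as appropriate". On size, Section 9.2 says: "The study is expected to enroll approximately 18 patients in total, with 6 in the placebo arm and 12 in the treatment arm", and "No formal statistical sample size calculations were performed; sample size is based on feasibility".

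For the healthy-volunteer study, Section 2.2.2 reports "a half-life of approximately 7 hours, and no indication of a change in the exposure on repeat dosing for 7 days".

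The detailed schedule (Table 2) has seven PK samples, predose to 10 hours, on Day 1 and on Day 5. Days 2, 3, 4, 6 and 7 each have a predose sample only.

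**The concern.** Two parts of the plan disagree. Sections 9.1 and 9.2 describe a purely descriptive study, while Section 9.4.4 prescribes a formal test.

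The form of the test matters too. With two days per participant, the ANOVA is a paired test that the ratio of AUCs equals 1. It does not give what a reader needs about accumulation, which is the size of the ratio and the range of values the data allow. Non-significance can reflect a small rise or an imprecise comparison. Significance can simply confirm a rise already expected from the half-life.

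Section 4.2.2 says that PK in patients with UC is not known, so this study would be the first source of an accumulation figure in that population. The point estimate could be worked out from the planned geometric means, but its precision could not.

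**Working it through.** **Inputs from the documents**

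- Participants informing the test: 12. Section 9.2 gives 12 on active drug and 6 on placebo, which matches 2:1 allocation of 18 (18 × 2/3 = 12). Under Section 8.4, "Samples collected from placebo-treated participants will not be analyzed in the first instance".
- Half-life: about 7 hours (Section 2.2.2, healthy volunteers).
- Dosing interval: 24 hours (Section 9.4.4).

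**Assumptions, because the documents give no figure**

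- Two-sided 5% level.
- Within-participant CV of AUC from 15% to 40%.
- True rises of 10%, 25% and 50% as illustrations. No relevant rise is defined in the plan.

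The plan has no power or precision figure of its own to reproduce.

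**Step 1. Ratio expected if clearance does not change.** Under one-compartment superposition, the steady-state to first-dose AUCtau ratio is 1/(1 − 2^(−24/7)) = 1/(1 − 0.0929) = 1.10. By the fifth dose it is (1 − 0.0929^5)/(1 − 0.0929), which is also 1.10, so Day 5 is in effect at steady state.

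**Step 2. Standard error.** On the log scale, sw = sqrt(ln(1 + CV²)) and SE = sw × sqrt(2/n), with n − 1 = 11 degrees of freedom. At CV 25%, sw = sqrt(ln 1.0625) = 0.246 and SE = 0.246 × sqrt(2/12) = 0.1005.

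**Step 3. Chance of missing a true rise.** Power comes from the noncentral t with noncentrality ln(ratio)/SE. For a 25% rise at CV 25%, this is 0.2231/0.1005 = 2.22, giving 53% power and a 47% miss rate.

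**Step 4. What a non-significant result leaves open.** The largest observed ratio that stays non-significant is exp(t0.975 × SE). Its upper 90% limit is exp((t0.975 + t0.95) × SE). With t0.975 = 2.201, t0.95 = 1.796 and CV 25%, these are exp(0.221) = 1.25 and exp(0.402) = 1.49.

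| CV | Miss 10% rise | Miss 25% rise | Miss 50% rise | Largest non-significant ratio | Its upper 90% limit | 90% CI factor |
|---|---|---|---|---|---|---|
| 15% | 70% | 9% | <1% | 1.14 | 1.28 | 1.12 |
| 20% | 81% | 29% | <1% | 1.20 | 1.38 | 1.16 |
| 25% | 86% | 47% | 4% | 1.25 | 1.49 | 1.20 |
| 30% | 89% | 60% | 13% | 1.30 | 1.61 | 1.24 |
| 40% | 91% | 75% | 35% | 1.41 | 1.88 | 1.33 |

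The last column is exp(t0.95 × SE), the factor by which the estimated ratio is multiplied and divided to give the 90% interval. A simulation of 200,000 replicates gave 71% power at CV 20% and 40% at CV 30% for a 25% rise, which agrees with the table.

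**Step 5. Where a miss becomes more likely than not.** With n = 12, this is above CV 26% for a 25% rise and above CV 49% for a 50% rise. With 10 evaluable participants, the threshold for a 25% rise falls to CV 23%.

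**Step 6. The comparison day.** Section 9.4.4 uses the day of the final dose, which is Day 7. Table 2 has only a predose PK sample that day, so neither AUCtau nor a partial AUC after the Day 7 dose can be derived from the current schedule. Days 1 and 5 have serial samples, and the predose samples on Days 2 and 6 close their 24-hour intervals.

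**The case against.** The strongest reply is that the test is secondary within its own paragraph. The plots come first, the test is introduced as an addition, and no decision rule is attached to it. Geometric means of AUC are planned. With complete pairs, the ratio of the two days' geometric means equals the geometric mean of the within-participant ratios, so the point estimate is effectively available. A population PK analysis is also planned, and Table 3 allows it as a route to the primary endpoint. No dose change or stopping criterion depends on accumulation.

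Most of this stands, and it limits the weight of the point. It does not supply an interval for the ratio in this study's own analysis. The population analysis pools several studies and is reported separately. The conflict with Sections 9.1 and 9.2 also remains.

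A reader might infer that a relevant rise would usually be missed. The documents do not support that, since they define neither a CV nor a relevant rise. On the figures above, a 25% rise is detected more often than not up to about CV 26%, and a 50% rise up to about CV 49%.

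A reader might also infer that accumulation is judged by the test alone and that non-significance will be reported as absence of accumulation. Section 9.4.4 does not say so, and Section 2.2.2 does not say how the healthy-volunteer conclusion was reached.

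The 1.10 figure is a reference point only. It assumes one-compartment kinetics and carries a healthy-volunteer half-life into patients.

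**Conclusion.** The point holds as a minor one. The only inferential output on accumulation is a test of ratio = 1, with no ratio, interval or margin, and it contradicts Sections 9.1 and 9.2. That contradiction rests on no assumption.

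The size of the problem does rest on assumptions: two-sided 5%, 12 evaluable participants and a within-participant CV that the documents do not give. Over CVs of 20% to 40%, a true 25% rise may be missed 29% to 75% of the time. At CV 25%, an observed ratio of up to about 1.25 would be non-significant. The value of 1.49 is the upper 90% limit at the very edge of non-significance, so it is a worst case and does not describe non-significant results in general.

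The test also names a day for which the schedule provides no AUC.

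**What to change.** In Section 9.4.4, replace the statistical test with an estimate from the same model, for example:

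> *The accumulation ratio, defined as the geometric mean ratio (Day 5 to Day 1) of AUCtau, or of AUC0-t over the same interval on both days, and of Cmax, will be presented with its 90% confidence interval from the log-scale ANOVA with terms for participant and day. It will be read descriptively against the ratio predicted by superposition from the Day 1 data. Absence of accumulation will not be concluded from a p-value.*

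Day 5 is used here because it is the only later day with a serial profile in Table 2. If the sponsor wants Day 7, the schedule needs serial samples that day; either way, Section 9.4.4 and Table 2 must agree. For AUCtau the superposition reference is about 1.10 at a 7-hour half-life. For Cmax or a partial AUC it should be computed from the Day 1 profile.

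This makes Section 9.4.4 consistent with Sections 9.1 and 9.2, since nothing is tested. If the sponsor prefers to keep the test, those two sections need an exception, and the ratio and interval should still be reported beside it.

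The cost is a few sentences, with the same model and, for Day 5, the same samples. The downside is that the interval may be wide: the estimate multiplied and divided by about 1.16 at CV 20% and 1.33 at CV 40%.

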| **Urinalysis** | **x** | **x** |  |  |  |  | **x** |  | **x** | **x** | **x** | **x** |
| **Pregnancy Test (WOCBP only)** | **x** | **x** |  |  |  |  |  |  |  |  |  | **x** |
| **Rectal biopsy** |  | **x d** |  |  |  |  |  |  | **x** |  | **x** |  |
| **Stool** | **x** | **x e** | **x f** | **x f** | **x f** | **x f** | **x f** | **x f** | **x f** |  | **x f** | **x** |
| **Clinical Genotyping** |  | **x g** |  |  |  |  |  |  |  |  |  |  |
| **PK Sample** |  |  | **7 b** | **x h** | **x** | **x** | **7 b** | **x h** | **x** | **x** | **6 c** | **x** |
| **ex-vivo cytokine release** |  |  | **7 b** | **x h** |  |  | **7 b** | **x h** | **x** |  | **6 c** | **x** |
| **Soluble PD biomarkers (serum / plasma)** |  | **x** | **x i** |  |  |  | **x i** |  | **x i** |  | **x i** | **x** |
| **Research Biosample Repository (RBR) Consent** | **Optional: If patients agrees to donate left over samples: preferred at day 1 but can be collected any tim e during the study** | | | | | | | | | | |  |
| **Exploratory Safety Sample** |  | **x** | **In case of Liver Function Test Abnormalities (see section 8.2.8)** | | | | | | | | |  |
| **Adverse Events or Intercurrent Illness** |  | **any time** | | | | | | | | | | |

a) In case of positive hepatitis B virus (HBV) serology (Anti-HBcAb positive) and negative PCR test at baseline (BL), the PCR test must be repeated at follow-up to exclude reactivation of HBV.

b) Predose, 30 min, 1 hr, 2 hr, 4 hr, 6 hr, 10 hr.

c) Predose, 30min, 1hr, 2hr, 4hr, 6hr. If the visit is an “Unscheduled

Visit” the post-dose sample needs to be taken only if the study treatment was taken.

d) Rectal biopsy up to Day −3 is acceptable. e) Prior to biopsy.

f) If available.

g) If missed on Day −1, the sample can be taken any day.

h) Pre-dose (.e.g., 24 hrs after the first study treatment administration or on Day 6).

i) 6 hr post-dose. If visit is an “Unscheduled Visit” the post-dose sample needs to be taken only if the study treatment was taken.

RO7486967**—F. Hoffmann-La Roche Ltd**

18/Protocol BP43099, Version 3

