**Table 2 Schedule of Activities - Detailed Table**

| **Day**  Vers ion  2021-09-06 | **Schedule**  **Time (h)** | **ECG** | **Vital signs** | **Stool** | **Rectal biopsy** | **Clinical**  **Genotyping** | **PK Sample** | **ex-vivo cytokine release** | **Soluble PD biomarkers (serum / plasma)** | **Exploratory Safety Sample** |
| --- | --- | --- | --- | --- | --- | --- | --- | --- | --- | --- |
| **Screening** |  | x | x | x |  |  |  |  |  |  |
| **Day -1** |  |  | x | x | x | x |  |  | x | x |
| **Day 1** | **any time** |  |  | x |  |  |  |  |  | Any Time in Case of Liver Function Test Abnormalities (see section 8.2.8) |
| **Day 1** | **predose** | x | x |  |  |  | x | x |  |  |
| **Day 1** | **30 min ± 5 min** | x | x |  |  |  | x | x |  |  |
| **Day 1** | **1 hr ± 5 min** | x | x |  |  |  | x | x |  |  |
| **Day 1** | **2 hr ± 10 min** | x | x |  |  |  | x | x |  |  |
| **Day 1** | **4 hr ± 10 min** | x | x |  |  |  | x | x |  |  |
| **Day 1** | **6 hr ± 10** | x | x |  |  |  | x | x | x |  |
| **Day 1** | **10 hr ± 30 min** | x | x |  |  |  | x | x |  |  |
| **Day 2** | **any time** |  |  | x |  |  |  |  |  |  |
| **Day 2** | **predose** |  | x |  |  |  | x | x |  |  |
| **Day 2** | **6 hr ± 10** |  |  |  |  |  |  |  |  |  |
| **Day 3** | **any time** |  |  | x |  |  |  |  |  |  |
| **Day 3** | **predose** |  | x |  |  |  | x |  |  |  |
| **Day 4** | **any time** |  |  | x |  |  |  |  |  |  |
| **Day 4** | **predose** |  | x |  |  |  | x |  |  |  |
| **Day 5** | **any time** |  |  | x |  |  |  |  |  |  |
| **Day 5** | **predose** | x | x |  |  |  | x | x |  |  |
| **Day 5** | **30 min ± 5 min** | x | x |  |  |  | x | x |  |  |
| **Day 5** | **1 hr ± 5 min** | x | x |  |  |  | x | x |  |  |
| **Day 5** | **2 hr ± 10 min** | x | x |  |  |  | x | x |  |  |
| **Day 5** | **4 hr ± 10 min** | x | x |  |  |  | x | x |  |  |
| **Day 5** | **6 hr ± 10** | x | x |  |  |  | x | x | x |  |
| **Day 5** | **10 hr ± 30 min** | x | x |  |  |  | x | x |  |  |
| **Day 6** | **any time** |  |  | x |  |  |  |  |  |  |
| **Day 6** | **predose** |  | x |  |  |  | x | x |  |  |
| **Day 7** | **predose** | x | x | x | x |  | x | x |  |  |
| **Day 7** | **6 hr ± 10** |  |  |  |  |  |  |  | x |  |
| **Unscheduled visit** |  | x | x | x |  |  | x | x | x |  |
| **Early Withdrawal** Assessments as deemed feasible |  | x | x | x | x |  | x | x | x |  |
| **FU** |  | x | x | x |  |  | x | x | x |  |

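### The accumulation analysis needs an AUC after the Day 7 dose, but the schedule takes no PK sample that could give one to any completer

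*Combined protocol and SAP*

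**What the plan says.** Section 9.4.4 sets out one model-based comparison for drug accumulation. It begins "In addition, AUCtau post the dose on Day 1, or alternatively a partial AUC0-t , will be tested statistically against AUCtau", and the comparator is the AUC "post the dose on the day of the final dose using an analysis of variance with terms in the model for participants and day", after a natural log transform. The same section provides a fallback: "a partial AUC0-t may be used instead of AUCinf or AUCtau should extrapolation to infinity or up to tau not be considered reliable".

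The PK sampling is set in Section 1.3. Table 1 marks a seven-sample series on Days 1 and 5 only, with the times in its footnote: "b) Predose, 30 min, 1 hr, 2 hr, 4 hr, 6 hr, 10 hr". The other dosing days each carry one sample. Table 2 puts the Day 7 sample in the row that begins "Day 7 | predose | x | x | x | x" and goes on to mark the PK column. Its only other Day 7 row, at 6 hours, marks soluble PD biomarkers and no PK sample. Section 8.8.2 makes predose the default for assessments on dosing days.

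Section 9.1 says that no hypotheses are to be tested, and Section 9.2 adds "No formal statistical analyses will be undertaken".

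**The concern.** The analysis text and the sampling schedule point to different days. The text asks for exposure after the last dose, while the schedule stops collecting PK on the last dosing day before that dose is given. An analyst who follows Section 9.4.4 literally has nothing to put on one side of the comparison.

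At stake is the plan's only model-based estimate of how exposure changes with repeat dosing in patients. Section 2.2.2 reports no sign of a change over seven days in healthy volunteers, and Section 4.2.2 says that the drug's PK in UC patients is not known. As written, someone must choose a substitute day, and perhaps a substitute AUC window, after concentrations are available. Section 6.3.1 lets PK data be received and cleaned on an ongoing basis, so the choice would not be made blind to the data.

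A smaller point sits in the same sentence. It promises a statistical test in a plan that elsewhere says there will be none.

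**Working it through.** The documents give no power, alpha or precision figure for this analysis, so there is no stated number to reproduce. The check is a count of samples, followed by a check that the proposed substitute day is suitable.

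**Inputs**
- Dosing days: 1 to 7 (Section 4.1.1; Table 1).
- Dosing interval: 24 h (Section 9.4.4).
- Series times: 0, 0.5, 1, 2, 4, 6 and 10 h on Days 1 and 5 (Table 1, footnote b; Table 2).
- Single predose samples: Days 2, 3, 4, 6 and 7 (Table 2).
- Follow-up: 7 ± 3 days after the last dose (Section 4.1.1).
- Half-life: about 7 h, in healthy volunteers (Section 2.2.2).
- Planned participants on RO7486967: 12 (Section 9.2).

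**Step 1. PK samples after the dose, up to and including 24 h**

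| Dose day | Samples within the day | 24 h sample | Total |
|---|---|---|---|
| 1 | 0.5, 1, 2, 4, 6, 10 h | Day 2 predose | 7 |
| 5 | 0.5, 1, 2, 4, 6, 10 h | Day 6 predose | 7 |
| 7 | none | none | 0 |

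**Step 2. Can the follow-up sample rescue Day 7?** The window is 4 to 10 days after the dose, or 96 to 240 h. At a 7 h half-life that is 96/7 = 13.7 to 240/7 = 34.3 half-lives. Under mono-exponential decline the fraction left at the earliest time is 2^(−96/7) = 0.000074, about 0.007%. Such a sample cannot define AUC0-24, nor any AUC0-t that matches Day 1.

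**Step 3. Consequence for the model.** A participant + day model needs values on both days. Completers supply up to 12 Day 1 values and no Day 7 values, so the day effect cannot be estimated for them. Replacing AUCtau by AUC0-t changes nothing, because any AUC0-t also needs samples after the dose.

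**Step 4. Is Day 5 a sound substitute?** Using a linear one-compartment approximation:
- Fraction of steady state at dose *n* = 1 − 2^(−24*n*/t½). For *n* = 5 and t½ = 7 h: 1 − 2^(−120/7) = 0.99999.
- Expected AUCtau ratio of steady state to Day 1 = 1/(1 − 2^(−24/t½)). For t½ = 7 h: 1/(1 − 0.0929) = 1.10.
- Because the half-life in patients is unknown, I assumed a range of 5 to 12 h. Over it, Day 5 is at 99.90% of steady state or more, and the expected ratio runs from 1.04 to 1.33.

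With 12 participants complete on both days, the model has 24 − 1 − 11 − 1 = 11 residual degrees of freedom. The same analysis is therefore estimable on Day 5, at what is effectively steady state.

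**The case against.** The strongest reply is that little is lost. Table 3 makes the PK parameters the primary endpoint, by non-compartmental and/or population methods, and accumulation is not a listed objective or endpoint. Steady-state Cmax, Tmax, AUCtau and CLss/F can all be taken from the Day 5 series and the Day 6 predose sample. Section 9.4.4 already summarises them with geometric means, so a descriptive comparison with Day 1 survives. All of this stands, and it limits the point to one supportive analysis. A reader might infer that the primary PK objective fails; the documents do not support that.

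Three further readings are tempting and should also be left aside:
- **That the test is underpowered or the wrong tool.** The plan makes no power claim, bases its sample size on feasibility, and nowhere says that a non-significant result would be read as absence of accumulation. Any power figure would rest on a within-subject CV that the documents do not give. The same log-scale model yields a ratio and an interval directly.
- **That the peak plots are also impossible.** The text says "apparent peak and trough (predose) after each dose administration will be plotted graphically" over the course of assessments. This can fairly be read as plotting peaks on the days with a series. It is loose wording, not a second failed analysis.
- **That nobody has a profile on the final-dose day.** A participant whose last dose fell on Day 1 or Day 5 could have the 0 to 10 h series, and an early withdrawal visit may give 0 to 6 h where feasible (Table 1, footnote c). These are non-completers, on days fixed by when they stopped. If the last dose was on Day 1, there is no second day to compare.

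Two possible escapes do not close the gap. Section 8.4 lets sampling times be amended on emerging data, but commits to no Day 7 sample after the dose. A population PK model could predict a Day 7 AUC, but that is a separate analysis, pooled across studies and reported elsewhere.

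**Conclusion.** The point holds in a limited form. The accumulation comparison in Section 9.4.4 cannot be computed for any completer from the scheduled samples: 0 of the 12 planned RO7486967 participants would have the second AUC if all complete treatment, and the stated fallback does not help. Tables 1 and 2 and Section 8.8.2 agree with one another, so this is not a misread table, and no other section resolves it.

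The sample count rests on no assumption beyond the schedule being followed as written. Only the suitability of Day 5 uses a model: linear one-compartment kinetics and a healthy-volunteer half-life of about 7 h. That conclusion is unchanged over the assumed range of 5 to 12 h. The trough plots, the listed Day 1 and steady-state parameters, and the population PK analysis are not affected.

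Separately, the promise of a statistical test is inconsistent with Sections 9.1 and 9.2. This is a matter of wording, which the same edit can settle.

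**What to change.** In Section 9.4.4:

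1. Replace the day of the final dose with Day 5. Define both AUCs as AUC0-24, with the next-day predose sample (Day 2 and Day 6) as the 24-hour point. If a partial AUC is used, apply the same *t* on both days; 10 h is the last time in each series.
2. Restrict the comparison to RO7486967 participants with both profiles. Section 8.4 already leaves placebo samples unanalysed in the first instance.
3. Replace the statistical test with the Day 5/Day 1 geometric mean ratio and its 90% confidence interval from the same log-scale participant + day model. Describe it as estimation, with no p-value. This brings the section into line with Sections 9.1 and 9.2.

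The cost is a wording change in one section, with no added samples, visits or participants. It should be made before PK data are analysed.

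The sponsor could instead keep Day 7 and add PK samples after that dose. A Day 7 AUCtau would then also need a 24-hour sample on Day 8, after the planned Day −1 to Day 7 stay. Since Day 5 is already effectively at steady state, that burden would buy little.
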